#### Control group

2.4.2

The control group will engage in a 10-min basic wheelchair exercise, followed by 20 min of watching landscape videos in their homes. The program will consist of three sessions per week over a total duration of 8 weeks.

### Outcome measures

2.5

A trained research assistant, blinded to group allocation, will conduct a series of assessments at three time points: baseline (T0), after the 8-week intervention program (T1), and 1 month post-intervention (T2). Socio-demographic variables, feasibility and acceptability indexes, and effect outcomes are included. The effect outcomes include primary outcomes (global cognitive function and depression) and secondary outcomes (neurocognitive domains, multimodal MRI findings, chronic pain, self-efficacy for exercise, and motor imagery ability). The assessments will be conducted during participants’ visits to the study site (University campus) (Table 1).

**Table 1 tab1:** Data collection schedule.

Assessment items	Study period			
	Enrollment	Allocation	Post-allocation	
	−T1	T0 Baseline	T1 Post-intervention	T2 1-month follow-up
Enrollment				
Eligibility screening	X			
Informed consent	X			
Allocation		X		
Assessments				
Socio-demographics and medical history		X		
Feasibility of the intervention		X		X
Acceptability of the intervention			X	
Intervention effectiveness				
Primary outcomes				
Global cognitive function		X	X	X
Depression		X	X	X
Secondary outcomes				
Cognitive domain-attention		X	X	X
Cognitive domain-executive function		X	X	X
Multimodal MRI findings		X	X	
Chronic pain		X	X	X
Self-efficacy for exercise		X	X	X
Motor imagery ability		X	X	X

MRI, magnetic resonance imaging.

#### Socio-demographics and injury characteristics

2.5.1

A self-designed form will gather participants’ socio-demographics and injury characteristics. This will encompass details including age, gender, marital status, occupation, exercise habits, educational level, mental medication, smoking and alcohol history, as well as information on the etiology, duration, neurological level of injury, complications, and American Spinal Injury Association (ASIA) Impairment Scale (AIS) category.

#### Feasibility and acceptability

2.5.2

The feasibility indices include the recruitment rate, which is the percentage of participants who give consent after determining their eligibility; the retention rate, which refers to the number of participants who complete the study divided by all participants who agree to consent; and the dropout rate, which is the number of participants who drop out after randomization divided by all participants who agree to consent (39). The acceptability of the intervention will be indicated by (1) adverse event records related to the AOMI intervention; (2) intervention satisfaction, evaluated through the 8-item Client Satisfaction Questionnaire with a four-point Likert scale (40) and a qualitative interview. The one-on-one interviews will be conducted by a research assistant trained in qualitative research and possessing a background in psychology; (3) adherence rate, measured as the percentage of participants completing a minimum of 60% of interventions, equivalent to at least 15 sessions.

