**Methods:**

This is an assessor-blinded, two-arm pilot randomized controlled trial with repeated measures (pre-, post-intervention, and 1-month follow-up). In total, 46 participants will be randomly assigned to either the intervention group, which will receive an 8-week AOMI intervention combined with basic wheelchair exercises, or the control group, which will watch landscape videos and perform basic wheelchair exercises. The feasibility of study procedures will be assessed by examining the recruitment, dropout, and retention rates. The acceptability of interventions will be evaluated by the adverse events record, satisfaction, and adherence rate. The primary outcomes of intervention effectiveness include global cognitive function and depression; secondary outcomes include neurocognitive domains, multimodal MRI findings, chronic pain, self-efficacy for exercise, and motor imagery ability.

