### Study design

2.1

A prospective, assessor-blinded, two-arm pilot randomized controlled trial with repeated measures (pre-, post-intervention, and 1-month follow-up) will be conducted to evaluate the effectiveness of the AOMI intervention among adults with SCI. In total, 46 participants will be randomly assigned to either the intervention group, which will receive an 8-week AOMI intervention combined with basic wheelchair exercises, or the control group, which will watch landscape videos and perform basic wheelchair exercises. Participants will undergo MRI scans at baseline and after the intervention. One-on-one qualitative interviews will be implemented post-intervention to collect participants’ perceptions of effectiveness, intervention acceptability, strengths, limitations, and suggestions for further improvement. Participants’ recruitment began in March 2025. This study protocol complies with the Standard Protocol Items: Recommendations for Interventional Trials Statement (SPIRIT) (24) and the Consolidated Standard of Reporting Trials Statement (CONSORT): extension to randomized pilot and feasibility trials (25) (Figure 1). The protocol was prospectively registered at ClinicalTrials.gov (NCT06708026).

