### Participants

2.2

Participants are being recruited from community centers and non-governmental organizations in Hong Kong using advertisement posters. Eligibility screening for potential participants is conducted via online questionnaires and phone calls. Final enrollment is confirmed during an in-person visit, where participants receive a detailed overview of the study, provide informed consent, and complete a baseline assessment.

Severe cognitive impairment could impair participants’ motor imagery abilities, which may interfere with the assessment of intervention efficacy (26). Therefore, subjects will be included if they are (1) aged 18 years or above; (2) diagnosed with SCI for over 6 months, as per the International Standards for the Neurological Classification of SCI, confirmed by computed tomography or MRI; (3) with stable spinal systems and good vital signs, and residing in the community; (4) having no contraindications for MRI scans (e.g., absence of metal or electronic implants, non-pregnant status, and absence of claustrophobia); (5) having a mobile Internet terminal (usually a smartphone) and proficient independent or caregiver-assisted usage; and (6) able to communicate in Cantonese/Chinese and to provide written informed consent.

The exclusion criteria are as follows: (1) severe impairments in hearing, verbal communication, or vision; (2) participation in concurrent psychotherapy, physiotherapy, exercise, or relaxation interventions; (3) physically active for over 150 min of moderate-intensity exercise per week; (4) diagnosed mental disorders or substance misuse; and (5) severe cognitive impairment [indicated by the Hong Kong Montreal Cognitive Assessment (HK-MoCA) score ≤ 18] (27). No restrictions will be imposed regarding the level, cause, or completeness of the spinal cord injury.

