### Sample size and sampling

2.6

The central limit theorem posits that a minimal sample size of 30–40 is enough for determining the mean, standard deviations, and 95% confidence intervals (58). This pilot RCT aims to assess the feasibility, acceptability, and preliminary effectiveness of the AOMI intervention, utilizing a generally acceptable sample size for preliminary analysis to evaluate intervention feasibility and estimate the between-group effect. Specifically, each study group will have 18 individuals to identify a standardized effect size of 0.40 with 80% power and a two-sided significance level of 5% (59). Taking into account a potential attrition rate of 20%, 23 participants per group (i.e., 46 participants in total) will be recruited by using convenience sampling. For one-on-one interviews, we will use a purposeful sampling of key informants, including those who completed at least 60% of the intervention sessions and those who did not, until we reach information saturation and find no relevant new codes in the data (60).

For MRI scans, a liberal threshold of *α* = 0.05 requires 24 participants (12 per group) to achieve 80% power at the single-voxel level for typical activations (61). To control error rates in multiple comparisons, doubling the number of participants is recommended to maintain this level of power. Due to the challenges of MRI data collection, each group will consist of a minimum of 12 participants undergoing pre- and post-intervention MRI scans. Notably, this sample size aligns with the median sample size observed in highly cited clinical fMRI studies published over the last three decades (62).

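### The dropout rate counts losses after randomisation but divides by everyone who consents, so it can only be understated and does not share a base with the planned 20% attrition

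*Protocol article*

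**What the plan says.** The abstract makes dropout one of three measures of feasibility: "The feasibility of study procedures will be assessed by examining the recruitment, dropout, and retention rates". Section 2.5.2 then defines it as "the dropout rate, which is the number of participants who drop out after randomization divided by all participants who agree to consent". The same sentence defines "the retention rate, which refers to the number of participants who complete the study divided by all participants who agree to consent".

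On the order of events, section 2.2 states: "Final enrollment is confirmed during an in-person visit, where participants receive a detailed overview of the study, provide informed consent, and complete a baseline assessment". Section 2.9 also has the consent form signed ahead of the baseline measures. Table 1 places consent in the −T1 column, and allocation together with the baseline measures in the T0 column. Section 2.3 allocates by minimisation on motor imagery ability, age and educational level, and Table 1 schedules motor imagery ability at T0. Allocation therefore needs data collected after consent.

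On numbers, section 2.1 says: "In total, 46 participants will be randomly assigned to either the intervention group". Section 2.6 says: "Taking into account a potential attrition rate of 20%, 23 participants per group (i.e., 46 participants in total) will be recruited".

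**The concern.** A proportion should have a numerator drawn from its denominator's population at risk. Here the event is dropping out after randomisation, so only randomised people are at risk, yet the denominator also admits people who signed consent and were never allocated. Each such person dilutes the rate.

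Three consequences follow:

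- The error runs in one direction only, towards a more favourable result on a named feasibility measure.
- The rate cannot be split by arm, because someone who was never allocated has no arm. A two-arm pilot of a home programme needs to see whether loss differs between the AOMI and landscape-video groups.
- The rate cannot be set directly against the 20% attrition used for planning, because that figure applies to those allocated.

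The Discussion says that the pilot's results will help to design a full-scale trial. A diluted dropout rate, used to inflate that trial's sample size, would inflate it too little.

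**Working it through.** **Inputs from the protocol article**

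- Randomised, R = 46 (section 2.1).
- Number per group before attrition = 18; planned attrition = 20%; recruited = 23 per group, 46 in total (section 2.6). I take the 18 as given; whether it suits its stated effect size is a separate matter.
- Number consenting, C: not stated. I vary it from 46 upwards as an assumption.

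**Step 1. Reproduce the plan's own attrition figure.** 18 / (1 − 0.20) = 22.5, rounded up to 23 per group, and 2 × 23 = 46. This matches section 2.6. It also shows the base of the 20%: the 46 are the people section 2.1 says will be randomised, so the planning rate is dropouts per person randomised.

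**Step 2. Express the defined rate in terms of the true one.** With D dropouts after randomisation:

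- true rate = D/R
- defined rate = D/C = (D/R) × (R/C)

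Consent precedes allocation, so C ≥ R and R/C ≤ 1. The defined rate can equal the true rate or fall below it, and cannot exceed it.

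**Step 3. Put in numbers.** 20% of 46 is 9.2, so take D = 9. The true rate is 9/46 = 19.6%.

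| Consenting (assumed) | Not randomised | Reported dropout | Shortfall (points) |
|---|---|---|---|
| 46 | 0 | 9/46 = 19.6% | 0 |
| 48 | 2 | 9/48 = 18.8% | 0.8 |
| 51 | 5 | 9/51 = 17.6% | 1.9 |
| 55 | 9 | 9/55 = 16.4% | 3.2 |

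Shortfalls are taken from unrounded rates.

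**Step 4. Compare with the 20% planning value.** With D = 10, the true rate is 10/46 = 21.7%, above 20%. With 51 consenters the plan reports 10/51 = 19.6%, below it. With 48 consenters it reports 10/48 = 20.8%, still above. The different base can change the comparison, but in this example two unallocated consenters are not enough.

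**Step 5. Effect on a later trial's inflation factor, 1/(1 − dropout), with D = 9.**

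- True rate: 46/37 = 1.243.
- 48 consenters: 48/39 = 1.231, about 1% lower.
- 55 consenters: 55/46 = 1.196, about 4% lower.

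**The case against.** The strongest reply is that the gap between consent and allocation is probably small. Section 2.5.2 counts consent after eligibility has been determined, section 2.9 has eligible people sign, and section 2.2 screens by questionnaire and telephone first. Consent and baseline share one visit. The article uses 46 both for those recruited and for those randomised, and forecasts no shortfall between the two. All of this stands, and it makes a bias of about one point or less more plausible than one of three. It does not close the gap: final enrolment is confirmed at that same visit, participants may withdraw at any time, and allocation waits for baseline data.

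Sampling error is also much larger than the bias: the 95% Wilson interval for 9/46 runs from roughly 11% to 33%. The article sets no feasibility threshold that the shift could cross, and its commitment to CONSORT for pilot trials should make losses per arm recoverable from the flow diagram. These points limit the harm. They do not justify a stated definition that needs the diagram to correct it.

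A reader might go further and infer that the retention definition is wrong as well, since it has the same denominator. The documents do not support that. Completers over consenters is a coherent measure of retention from consent, and its denominator errs towards a lower, less favourable figure. Nor is it an error in itself that the two rates fail to sum to 100%, given that dropout is explicitly limited to the period after randomisation.

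**Conclusion.** The point holds for the dropout denominator. As defined, the rate equals true post-randomisation dropout times randomised/consented. It is therefore understated whenever anyone who consents is not allocated and at least one allocated participant drops out. It has no by-arm version, and it does not share a base with the 20% attrition in section 2.6.

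The size depends on a number the article does not give. At 9 dropouts of 46 the understatement is zero if every consenter is randomised, 0.8 points with 48 consenters, 1.9 with 51 and 3.2 with 55, and the lower values are more likely. A reader might infer that the pilot's dropout result will be seriously misleading, or that the next trial would be badly undersized. Nothing in the article points to losses between consent and allocation large enough for that. This is a modest flaw in a stated rule, worth correcting because the error can only flatter the result and the correction is almost free.

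**What to change.** In section 2.5.2, define dropout as the number who drop out after randomisation divided by all participants randomised, overall and by arm. Report randomised/consented as a separate rate, so that loss before allocation is still visible. The existing retention rate may remain if it is labelled as retention from consent; report completers/randomised beside it, so that one retention figure complements dropout on the same base.

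The cost is one definition reworded. No new data are needed, since the numbers consenting, randomised and lost will be counted in any case, and the change can be made although recruitment has begun. The reported dropout rate may come out slightly less favourable.

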### Interventions

2.4

All participants will perform the same basic wheelchair exercises at home, following an instructional video. The video, which contains a set of low-intensity warm-up exercises, was developed by two experienced physiotherapists in Hong Kong (30). All participants will receive weekly phone calls to monitor progress and provide support during the training period. In order to avoid potential adverse events associated with the exercise (i.e., falls, joint pain, muscle strain, stress fracture, and exacerbation of existing injuries and disease symptomology) (31), the intensity of the workouts will be evaluated using the Borg ratings of perceived exertion (RPE), which should be maintained at less than 13 scores to ensure light to moderate intensity (32).

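### The adverse event indicator is limited to events related to AOMI, so as defined it cannot compare adverse events between two arms that share the same exercise

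*Protocol article*

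**What the plan says.** Section 2.5.2 (Feasibility and acceptability) names three indicators of acceptability: adverse events, satisfaction and adherence. The first is worded as "adverse event records related to the AOMI intervention", and this is the only definition of the adverse event measure in the Methods.

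The Methods paragraph of the abstract is broader: "The acceptability of interventions will be evaluated by the adverse events record, satisfaction, and adherence rate". It speaks of interventions in the plural and does not restrict events by cause.

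Section 2.4 (Interventions) states: "All participants will perform the same basic wheelchair exercises at home, following an instructional video". It then names "potential adverse events associated with the exercise (i.e., falls, joint pain, muscle strain, stress fracture, and exacerbation of existing injuries and disease symptomology". Section 2.4.2 describes the comparator: "The control group will engage in a 10-min basic wheelchair exercise, followed by 20 min of watching landscape videos in their homes". The control arm therefore has the exercise but no AOMI.

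Section 2.4 also provides weekly calls to everyone during training. Table 1 marks acceptability at the post-intervention visit only.

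**The concern.** Acceptability is part of the trial's primary aim, and adverse events are the first of its three indicators. In a randomised trial, the natural way to learn whether AOMI adds harm is to count events by the same rule in both arms and compare. A rule that admits an event only when it is tied to one arm's treatment gives up that comparison.

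This matters here because some relevant symptoms occur without any intervention. The Introduction describes chronic neuropathic pain as a frequent complication of spinal cord injury. For such symptoms, case-by-case attribution is a weak substitute for a concurrent control count.

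The harms that the protocol anticipates are also not clearly those that the indicator counts. The list in section 2.4 concerns the shared exercise, while the indicator concerns AOMI.

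**Working it through.** The plan gives no adverse event rate or planned event comparison, so there is no figure to reproduce. The check sets the definition against the content of each arm.

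**Inputs**
- Indicator: events related to the AOMI intervention (section 2.5.2).
- AOMI arm: 10 min exercise plus 20 min AOMI (section 2.4.1).
- Control arm: 10 min of the same exercise plus 20 min of landscape video (sections 2.4 and 2.4.2).
- Listed harms: "potential adverse events associated with the exercise" (section 2.4).
- Planned size: 23 per arm (section 2.6).

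**Step 1: two readings of the definition.** Reading (a) takes the AOMI intervention to be the imagery component. Reading (b) takes it to be everything the intervention arm receives.

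| Event | Arm | Counted under (a) | Counted under (b) | Counted if all events are recorded |
|---|---|---|---|---|
| Injury from the shared exercise | AOMI | no | yes | yes |
| Injury from the shared exercise | Control | no | no | yes |
| Symptom attributed to imagery | AOMI | yes | yes | yes |
| The same symptom | Control | no | no | yes |

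Under both readings the control column is empty by construction. Only the last column treats the arms alike.

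**Step 2: effect on a between-arm difference.** Suppose k participants in each arm of 23 have an exercise injury, so the true difference is zero.
- Reading (a): 0/23 − 0/23 = 0. The difference is right, but the burden of k/23 in each arm is not shown.
- Reading (b): k/23 − 0/23 = k/23. The difference is spurious and unfavourable to AOMI. Each such participant adds 1/23 = 4.3 percentage points.
- All events recorded: k/23 − k/23 = 0.

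For a symptom that also arises without AOMI, reading (a) subtracts a control count of zero whatever happened in that arm. The result is a one-arm count.

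**Step 3: other text.** Section 2.9 covers the evaluation, management and referral of participants with safety concerns. It does not define a count by arm. The abstract's unrestricted wording would permit a comparison, but it conflicts with section 2.5.2.

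**The case against.** The strongest reply is that section 2.5.2 defines an acceptability indicator, not the trial's whole safety record. It does not say that other events are ignored. The abstract is unrestricted, the weekly calls reach both arms, and section 2.9 covers safety concerns in any participant. A condensed article may also leave event forms, coding and tabulation to the full protocol. This stands, and it limits the point to the indicator as worded. It does not remove the point, because the article states a restriction that fails under either reading and differs from its own abstract.

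A reader might infer more than the documents support:
- *Harms cannot be compared at all.* This goes too far. Pain is measured in both arms at all three time points with the Brief Pain Inventory. That covers pain, but not falls, strain or fracture as events.
- *Relatedness will be judged by staff who know the allocation.* No section says who judges it. Section 2.3 says only which roles are unblinded.
- *Asking about AOMI-related events will unblind the assessor before follow-up.* Section 2.5 says "A trained research assistant, blinded to group allocation, will conduct a series of assessments at three time points" and groups the acceptability indexes with the other measures, but it does not say that this person elicits events. Section 2.5.2 speaks of records, which may be kept elsewhere, and the mark in Table 1 may show only when acceptability is summarised.
- *Fatigue and dizziness are common in this population.* The article documents this for pain only.
- *The defect can be sized by the upper bound for no events in 23.* That bound is 1 − 0.05^(1/23) = 12.2% one-sided, or about 13% by the rule of three. It reflects arm size and would be the same if all events were recorded.

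It is also fair that 23 per arm gives an imprecise comparison. That argues for descriptive reporting, not for a rule that leaves the control arm out.

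**Conclusion.** The point holds for the adverse event indicator as section 2.5.2 defines it. Followed as written, it gives no valid between-arm comparison of adverse events. Either control participants cannot contribute and exercise harms vanish from both arms, or exercise harms count in the AOMI arm alone. The definition is also narrower than the abstract, so the two need to be reconciled.

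The size of any distortion cannot be estimated, because the article gives no event rates. The figure of 4.3 percentage points per affected participant assumes reading (b), 23 per arm and equal true occurrence in both arms. The conclusion does not depend on who judges relatedness or on any loss of blinding. It affects one indicator of a primary aim and leaves the analysis of cognition and depression untouched.

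**What to change.** Align section 2.5.2 with the abstract:
- Record all adverse events in both arms, whatever the suspected cause, using the same question.
- Ask it at the weekly calls already planned for all participants, and again at the 1-month follow-up. Have it asked by staff other than the blinded outcome assessor. This is a simple precaution and implies no finding that blinding is compromised now.
- Report by arm the number and percentage of participants with any event and with any serious event, each with a 95% CI, as description and not as a test.
- Keep relatedness to AOMI or to the exercise as a secondary label on each record.

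The cost is one scripted question, a reworded definition and a few more records to enter. Treatment, visits and sample size do not change. Recruitment began in March 2025, so the change is best made soon: events not captured as they occur may be hard to recover later.
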